#### Secondary Outcomes

##### Smoking

Secondary outcomes assessed at 2-, 5-, and 8-months post baseline will include:
7-day point prevalence abstinence, based on “Have you smoked at least part of a cigarette in the last 7 days?”Reported cigarettes smoked per day (for daily smokers) or cigarettes per week (for non-daily smokers).Expenditure on cigarettes.Number of quit attempts of 24 h or more, 1 week or more, and 1 month or more in the previous 3 months or since last assessed.Time to relapse: in those who do relapse will be determined by asking when they first smoked after a quit attempt.Number of subsequent quit attempts among those who relapsed.Hospitalizations and other intensive health service use.Financial stress questions adapted from Siahpush and Carlin (46).Productivity impacts (time off work or other duties).

Heaviness of Smoking Index (HSI): Nicotine dependence is assessed using this two item Index (47, 48). It uses a six-point scale calculated from the number of cigarettes smoked per day (1–10, 11–20, 21–30, 31+) and the time to first cigarette after waking (≤5, 6–30, 31–60, and 61+ min). Nicotine dependence is then categorized into a three-category variable: low (0–1), medium (2–4), and high (5–6). The HSI has been found to have good reliability and reasonable predictive validity (49).

Cravings: assessed by one item taken from the International Tobacco Control (ITC) Four Country Survey (50, 51), “Currently, how often do you get strong cravings to smoke tobacco?” with the response options of: (1) Hourly or more often; (2) Several times per day; (3) At least once a day; and (4) Less than daily. Difficulty in coping with situations in which smoking is not allowed is also assessed, on a 4-point Likert Scale from “very,” “moderately,” “mildly” to “not at all difficult.”

Withdrawal symptoms: as assessed by the Minnesota Nicotine Withdrawal Scale [MNWS; (52)], an eight item ordinal scale rating withdrawal symptoms from 0 (not present) to 3 (severe). At baseline the MNWS is administered, with two symptoms (concentration and appetite) assessed at follow-up. The MNWS has been shown to have good reliability and predictive validity (53).

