**SMOKING MEASURES:**				
Current smoking and quit attempts	X	X	X	X
7 day point prevalence abstinence (self-reported)		X	X	X
6 month prolonged abstinence (primary outcome)				X
CO Monitoring (those reporting abstinence)				A
Heaviness of Smoking Index	X	S	S	S
Tobacco types	X			
Cost	X	S	S	S
History (age first smoked)	X			
Social influences	X			
Cravings	X	X	X	X
Smoking use motives	X			
Situations not allowed to smoke		X	X	X
Goal	X			
Motivation to quit	X	S	S	S
Confidence to quit	X			
Self-efficacy		X	X	X
Products/services to help quit (including NRT, Quitline)	X	X	X	X
Nicotine replacement products (helpfulness, likely use)	X			
Counseling preference (in person or telephone)	X			
Minnesota Nicotine Withdrawal Scale (only two items in follow ups)	X	X	X	X

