**Key**

* *If not captured at previous assessment*.

***E** Extracted data*.

***S** Current smokers*.

***$** If used Quitline*.

***A** Those reporting abstinence*.

***I** Selected subsample*.

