### Statistical Methods

#### Primary and Secondary Outcomes

Independent and blinded statisticians from the CReDITSS Unit at the Hunter Medical Research Institute, Australia, supervised by [name], will conduct analyses of the primary and secondary outcomes.

Analyses will be carried out using a cluster randomized trial framework where the individuals (*n* = 150) are treated as clusters that contribute only one person, the short-term residential programs are clusters that contribute an average of 15 people each (10 programs × 15 people/program = 150 total) and the long-term programs are clusters that contribute 10 people each (6 programs × 10 people/program = 60). We will use a generalized linear mixed model (linear regression for continuous outcomes and logistic regression for dichotomous outcomes) to handle the clustering and the repeated measures at baseline, 2-, 5-, and 8-months; individuals will be modeled as random effects, cluster as a random effect, and group assignment as a fixed effect. Mixed models allow for missing data for the primary intention to treat analysis, but a sensitivity analysis using a worst case scenario (baseline value for continuous outcomes or relapse for dichotomous outcomes in case of missing value) will also be carried out.

Intervention participants who do not complete the intervention, and participants who miss an assessment follow-up time point, will be kept in the study and contacted for later assessments (unless they choose to withdraw from the follow-up assessments).

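### Time to relapse and later quit attempts are limited to relapsers, and follow-up expenditure and Heaviness of Smoking Index to current smokers, so arm comparisons on them leave out people who stay quit

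*Protocol article*

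**What the plan says.** Two outcomes in the smoking list under Secondary Outcomes are restricted to people who relapse: "Time to relapse: in those who do relapse will be determined by asking when they first smoked after a quit attempt" and "Number of subsequent quit attempts among those who relapsed". No censoring is described for people who quit and do not relapse.

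Two more are restricted by collection. In Table 1 the index row reads "Heaviness of Smoking Index X S S S", and the Cost row carries the same codes. The key defines S as "Current smokers". Both measures are therefore taken from everyone at baseline but only from smokers at 2, 5 and 8 months. Smoking status is asked of everyone: "Current smoking and quit attempts X X X X".

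Statistical Methods analyses the secondary outcomes by mixed models (linear or logistic) with group as a fixed effect. Missing data in the main intention-to-treat analysis are left to the mixed model. A separate worst-case sensitivity analysis substitutes "baseline value for continuous outcomes or relapse for dichotomous outcomes in case of missing value". Aims and Anticipated Results both name expenditure among the effects of Quitlink to be examined.

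**The concern.** Being a smoker at 5 months, or having relapsed after a quit attempt, is decided after randomisation, and Quitlink is designed to alter it. Arms compared within such a subset are no longer the randomised arms. The people removed are the treatment successes, and more of them are removed from the intervention arm if Quitlink works.

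For expenditure, the benefit from stopping altogether drops out of the comparison. For time to relapse, the longest durations are missing. If Quitlink turns early relapse into lasting abstinence, the people it helped leave the analysis and only those it did not help are timed.

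Leaving quitters blank in the mixed model does not repair this. The model would fill the gap implicitly from the values of people who still smoke, although the value is absent because the person stopped.

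**Working it through.** **Inputs.** Sample Size Determination gives prolonged abstinence of 1% (control) and 8% (intervention), 134 per arm, 30% attrition and 191 per arm. Allocation is 1:1. Two-sided testing is assumed, since the article does not state it.

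**The plan's own figure.** With the unpooled normal approximation:

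n = (1.96 + 0.8416)² × (0.01 × 0.99 + 0.08 × 0.92) / 0.07² = 133.75, so 134 per arm.

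133.75 / 0.70 = 191.1, stated as 191. The figures reproduce and are not in dispute; they are used here only to size the excluded group.

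**Who is left out.** Sustained quitters among the 134 analysed per arm:
- control: 134 × 0.01 = 1.3
- intervention: 134 × 0.08 = 10.7

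**Expenditure.** Assume:
- a baseline mean of 100 in both arms
- quitters had average baseline spending and now spend 0
- continuing smokers have mean *s* at follow-up in both arms
- q₁ and q₀ are the proportions quit in the intervention and control arms

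Intervention minus control is then:
- quitters coded as 0: −(q₁ − q₀) × s
- current smokers only: s − s = 0
- quitters given their baseline value: (q₁ − q₀) × (100 − s)

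| Quit, control / intervention | s | Quitters = 0 | Smokers only | Quitters = baseline |
|---|---|---|---|---|
| 1% / 8% | 100 | −7.0 | 0 | 0 |
| 1% / 8% | 80 | −5.6 | 0 | +1.4 |
| 5% / 15% | 80 | −8.0 | 0 | +2.0 |
| 10% / 25% | 80 | −12.0 | 0 | +3.0 |

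The first row uses the plan's rates and no change in continuing smokers. The others are illustrations: s = 80 is assumed throughout them, and the last two rows also assume higher quit rates, because abstinence at a single visit can exceed six-month sustained abstinence. In every row the smokers-only comparison misses the whole effect. If quitters were given baseline values while smokers cut down, the sign would reverse.

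**Time to relapse and later attempts.** No arithmetic is needed. Read literally, the definitions exclude everyone who quits and does not relapse, expected at 8% against 1%. They also exclude everyone who never quits.

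**The case against.** The strongest reply is that the S code is questionnaire routing, not an analysis rule. Smoking status and 7-day abstinence are asked of everyone, so zero spending can be derived for a quitter, and an analysis plan that is not shown may do so. The time-to-relapse sentence can be read as saying how the relapse date is obtained, with censoring left for later. The HSI has no natural value in someone who does not smoke. Much of this stands. It narrows the point to the restrictions that the article actually states, and it means that the repair needs no new data.

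A reader might go further and infer any of four things that the document does not support:

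- **Missing values revert to baseline as a general rule.** They do so only in the worst-case sensitivity analysis. The rule cannot apply to time to relapse, which has no baseline value.
- **Quitters are scored as unchanged.** The article never says that a known quitter's skipped item counts as missing. It also does not exempt that item, so this is a risk in the sensitivity analysis and not a stated step.
- **Cigarette consumption excludes abstainers.** The wording "Reported cigarettes smoked per day (for daily smokers) or cigarettes per week (for non-daily smokers" sets the reporting unit, and current smoking is asked of everyone. What remains is that two units are used and no value is stated for abstainers.
- **Motivation is an equal instance.** The row reads "Motivation to quit X S S S", and Aims names motivation, but it is listed among covariate or process measures and its follow-up question makes sense only for smokers.

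**Conclusion.** The point holds for four listed secondary outcomes: time to relapse and later quit attempts, restricted to relapsers by definition, and expenditure and HSI, restricted to current smokers by collection. Arm comparisons on them as written are not randomised comparisons, and they leave out sustained quitters unequally.

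For expenditure, the loss at the plan's own rates is about 7% of the baseline mean, reported as 0. This rests on continuing smokers not changing and on quitters having average baseline spending. It also takes six-month sustained abstinence as the proportion with no spending. Other assumptions change the size.

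Time to relapse and expenditure matter most. For HSI and later attempts, the issue is mainly how the result is labelled. The primary outcome and 7-day abstinence cover all participants and are untouched, so this should be corrected but does not threaten the main conclusion.

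**What to change.** - Set expenditure to 0 at any follow-up where the participant reports abstinence. Do the same for consumption, with daily and non-daily smokers on one scale (cigarettes per week divided by 7).
- Apply the baseline-value sensitivity rule only to people not interviewed, and state that known quitters are exempt.
- Analyse time to relapse from the quit date in everyone who quits, censoring those who have not relapsed at last contact. Because quitting itself happens after randomisation, add an all-randomised version with time 0 for those who never quit.
- Report HSI among continuing smokers, and later attempts among relapsers, as descriptive and not as randomised comparisons.

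The cost is a few derivation rules and one additional time-to-event analysis. Smoking status and quit attempts are already collected from everyone, so no new data are required.

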#### Primary Outcome

The primary outcome is defined as continued abstinence from smoking since the end of the treatment period, i.e., 6 months sustained abstinence, with no relapse (defined as 7+ days of continuous smoking, and no reported smoking in the last week), with biochemical verification at 8-month follow-up. Sustained abstinence will be assessed via the following question: “When did you last smoke a cigarette, even a puff?” If a participant reports prolonged abstinence at the 8 month follow up, and no smoking in the last week, they will be asked to attend a face to face visit to complete CO testing for objective validation using a Micro+ Smokelyzer, with a reading of 8 ppm or higher defined as indicative of recent smoking.

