#### Participant Selection

At 2 months, 30 participants will be interviewed (15 in each study arm, with cessation outcomes balanced across groups to negate any potential therapeutic effect of the additional qualitative interviews). The majority of the interviews (~10 per arm) will be with participants who have either not reduced smoking levels or have made only some reduction in smoking (<50%). Having a mix of those who have engaged with the intervention (attended 4+ Quitline sessions; or engaged in other treatments) and those who have not engaged or under-engaged (1–3 sessions) will enable identification of both barriers to engagement and barriers to change.

At 5 months, another 30 participants will be interviewed (15 per treatment arm, balanced for smoking outcomes). The majority (~10 per arm) will be “relapsers” (defined as those who have reduced consumption by 50–100% at 2 months but have resumed or increased use by 5 months), to allow a focus on medium term barriers to cessation maintenance, again with a mix of those who are engaged and those who are non- or under-engaged.

At 8 months, 12 participants will be interviewed (no balancing required as this is after primary endpoint collection), including ~6 who have relapsed (in order to focus on longer term barriers to cessation maintenance). At each time point, interviews will also be conducted with people who have successfully quit and maintained cessation to determine whether those who are successful face the same barriers as others but overcome them, and/or use the intervention in different ways. Participants in the qualitative study will be remunerated $40 for participation in individual interviews expected to take ~45 min.

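### Time to relapse is restricted to people who relapse but dated from their first smoking after a quit attempt, which under the article's own definition of relapse need not be the relapse

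*Protocol article*

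**What the plan says.** Under Outcome Measures, Primary Outcome, the article requires sustained abstinence "with no relapse (defined as 7+ days of continuous smoking, and no reported smoking in the last week". This is the only definition of relapse given for an outcome. The clause about the last week reads as a further condition on abstinence, so relapse itself means a run of at least seven days of smoking, and a shorter lapse is not a relapse.

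Under Secondary Outcomes, Smoking, the population and the dating question are both fixed in one item: time to relapse "in those who do relapse will be determined by asking when they first smoked after a quit attempt". The next item in the list, "Number of subsequent quit attempts among those who relapsed", depends on the same classification.

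Two other places bear on the point. The question behind the primary outcome is "When did you last smoke a cigarette, even a puff", which dates the latest cigarette. Under Participant Selection for the qualitative interviews, relapsers are "defined as those who have reduced consumption by 50–100% at 2 months but have resumed or increased use by 5 months"; that definition serves interview sampling only.

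**The concern.** A time-to-event outcome needs one event that both decides who has it and supplies the date. Here the deciding event appears to be a run of seven or more smoking days, while the date is that of the first cigarette after a quit attempt. These coincide only when the first cigarette starts the run. A person who slips, recovers and relapses later can be given the date of the slip. A person who slips and never relapses has a first-smoking date that is not used.

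At stake is the interpretation of one secondary outcome. A result reported as time to relapse could partly be time to first lapse, measured only in those who later relapsed. Two analysts could also classify the same people differently, for this item and for the count of later quit attempts.

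**Working it through.** The article gives no figure for this outcome, so there is nothing to reproduce. The check sets the definitions side by side and applies them to simple records.

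**Definitions, for one index quit attempt at day 0.** Let L be the day of first smoking after the attempt and R the first day of the first run of seven or more smoking days. The Primary Outcome definition makes R the relapse. The secondary outcome admits people for whom R exists and records L. The first day of a run is itself a smoking day, so L ≤ R always. Equality holds only if the first cigarette starts the run. Otherwise the recorded time is short by R − L.

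**Three constructed records.**

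| Record | L | R | Relapse = run of 7 or more days | Relapse = any smoking |
|---|---|---|---|---|
| Daily smoking from day 5 | 5 | 5 | Included, recorded as 5, correct | Included at 5 |
| One cigarette on day 5, abstinent again, daily smoking from day 60 | 5 | 60 | Included, recorded as 5; relapse starts on day 60 | Included at 5 |
| One cigarette on day 5, no later run | 5 | none | Excluded | Included at 5 |

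In the second record the gap is 60 − 5 = 55 days. This takes day 0 as the index attempt. If the abstinence after day 5 counts as a new attempt and becomes the index, first smoking after it falls on day 60 and agrees with the relapse. The item does not say which attempt is meant.

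**Can the date of the run be recovered?** Not from the questions the article describes: one dates first smoking after an attempt, the other the most recent cigarette.

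**How large could the understatement be?** This needs the distribution of R − L, which the documents do not give. The following illustration rests wholly on assumptions. Let L be exponential with mean 14 days. Let a share p of relapsers have R = L, and let the rest have R = L + G, with G exponential with mean g days.

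- Median of L = 14 × ln 2 = 9.7 days, whatever p and g are.
- For g ≠ 14, P(R > t) = p·exp(−t/14) + (1 − p)·[g·exp(−t/g) − 14·exp(−t/14)]/(g − 14). For g = 14 the bracketed term becomes exp(−t/14)·(1 + t/14). Setting this to 0.5 gives the median of R.
- Understatement of the median = 1 − 9.7/median(R).

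| p | Median R, g = 7 | Median R, g = 60 | Understatement |
|---|---|---|---|
| 0.5 | 13.5 | 24.0 | 28% to about 60% |
| 0.8 | 11.2 | 13.1 | 13% to 26% |
| 0.9 | 10.4 | 11.2 | 7% to 13% |
| 1.0 | 9.7 | 9.7 | 0% |

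The sign is fixed by L ≤ R. The size runs from nothing to more than half, depending mainly on p, which is unknown.

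**The case against.** The strongest reply is that the seven-day definition is imported. It stands in a parenthesis within the primary outcome, which concerns abstinence since the end of treatment. The secondary item does not invoke it, starts from a quit attempt, and belongs to a list that counts attempts from 24 hours upward. The article uses the word loosely elsewhere, including the consumption-based relapsers of the qualitative study. If relapse in this item means any return to smoking, event and date agree and the third record is counted at day 5. That reading is possible. It removes the mismatch only by giving one word two meanings in neighbouring outcome definitions without saying so, so the text needs reconciling either way.

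It can also be said that the index attempt is a detail for the full protocol or analysis plan. That is fair for the index attempt. It does not cover the population and the dating question, which the article states.

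Some stronger readings are tempting, and the documents do not support them:

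- **A particular size of bias.** A reader might infer that time to relapse is understated by 28% to 60%. That range needs half of relapsers to relapse at once, which is an assumption.
- **Bias against the intervention arm.** A reader might infer this because Quitlink allows extra calls for crises around relapse. No data show that the interval between slip and relapse would differ by arm.
- **That the trial cannot detect recovery from slips.** It can elsewhere: the primary outcome tolerates lapses under seven days, and quit attempts by duration and 7-day point prevalence abstinence are also collected.

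Finally, time to relapse does not appear in the abstract, the aims or the anticipated results, so it is a minor outcome.

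**Conclusion.** The point holds as an inconsistency in one secondary outcome. Taking the Primary Outcome definition of relapse and a single index quit attempt, the rule selects people on a run of seven or more smoking days and dates them at a first lapse, on the same day or earlier. People who lapse without relapsing are left out. If the item means any smoking, its wording conflicts with the Primary Outcome section instead.

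The direction of the error follows from the definitions. Its size cannot be determined from the documents, and nothing supports a claim about a difference between arms. The primary outcome and the sample size are unaffected. The count of later quit attempts among relapsers shares the ambiguity about who has relapsed, but not the dating problem. The correction is worthwhile mainly because it is cheap.

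**What to change.** **Simplest option.** Rename the outcome *time to first lapse*. Name the index quit attempt (for example, the first attempt of 24 hours or more after baseline). Count any smoking after that attempt as the event. Include everyone who made a quit attempt, censoring those who did not smoke at their last assessment. The first-smoking question stays as it is but is put to everyone with an attempt. The cost is a change of wording, plus making sure the start date of the index attempt is recorded.

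**If time to relapse is wanted.** Add one question dating the first day of the first run of seven or more smoking days after the index attempt. Again include everyone who made an attempt and censor those who did not relapse. Re-dating alone is not enough, because an analysis of relapsers only is confined to a group formed after randomization. The cost is one more interview item, with recall error over the interval since the last assessment.

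Under either option, state once what relapse means and use it for the later-quit-attempts item too. Making a quit attempt is itself a post-randomization event, so the number who made one should be reported by arm beside the result, and the comparison read with that in mind.

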## Aims

The primary aim of this research is to test the effectiveness of the Quitlink intervention for smoking cessation among SSMI. It is hypothesized that the intervention will be associated with higher rates of continued abstinence from smoking following the end of the treatment period, relative to the control condition. Secondary aims are to examine: (i) the cost-effectiveness of Quitlink compared to the control condition; (ii) barriers and enablers to making and sustaining quit attempts using qualitative methods so as to better understand why cessation rates among SSMI remain low; and (iii) the effect of Quitlink on 7-day point prevalence abstinence at 8-months, and effects on reported cigarette consumption, rates of quit attempts, nicotine withdrawal, expenditure on cigarettes, smoking cessation motivation and self-efficacy, mental health, quality of life and alcohol, and cannabis use. We will also assess process measures such as extent of use of advice and use of quit smoking medications (regardless of condition). The cost-effectiveness protocol is described elsewhere by Sweeney et al. (in submission) and the nested qualitative study and outcome measures are described below.

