##### Covariate or process measures

Demographic variables (e.g., gender and age).

History of tobacco smoking and quitting.

Types of tobacco used.

Social influences on smoking, e.g., lives with other smokers.

Smoking Use Motives: As part of this trial self-reported reasons for smoking are assessed using a modified version of the Drinking Motives Questionnaire (57), with additional items developed by Spencer et al. (58) to explore the use of substances to alleviate psychotic symptoms (positive and negative).

At baseline, participants will be asked whether they have a preference for in person or telephone counseling. They will also be asked to rate the likely helpfulness of NRT to long term quitting (not at all, some, moderately, extremely) and likelihood of use in the longer term (not at all, some, moderately, extremely).

Motivation to quit: assessed by a single question adapted from Crittenden et al. (59), “How much do you want to quit smoking?” (not at all, a little, some, very much). At follow-up assessments, “Are you trying to quit smoking altogether or are you planning to keep smoking at this level?”

Confidence to quit (at baseline) is measured by the following question: “How confident are you that you can stop smoking for good in the next 2 months if you wanted to?” (not at all, somewhat, moderately, very, extremely).

Self-efficacy in quitting is measured by the following question adapted from Perkins et al. (60): “How confident are you that you will not smoke at all tomorrow?” (not at all, somewhat, moderately, very, extremely). For those who quit at follow-up, “How confident are you that you will be able to stay quit long-term and become a permanent ex-smoker?” (not at all, somewhat, moderately, very, extremely).

Medications: Changes in use of prescribed psychotropicmedication.

Medication side effects: At baseline, participants will be asked to rate 10 symptoms during the past week (e.g., dry mouth, increased thirst) on an ordinal scale from 0 (not present) to 3 (severe). This measure is informed by the most common adverse side effects of psychiatric medications as identified in the Side Effect Survey, which has demonstrated validity and reliability (61).

Treatment received (use of NRT and Quitline—number and length of calls).

Objective data on service use (number and length of calls) will be extracted from the Quitline database for all participants (as some control participants may have self-referred).

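### Motivation and self-efficacy are named as secondary effects, but the items collected do not support the baseline-to-8-month repeated-measures model

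*Protocol article*

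**What the plan says.** **Status of the measures.** The Aims list "smoking cessation motivation and self-efficacy, mental health, quality of life" among the effects to be examined. Anticipated Results counts motivation and self-efficacy among the secondary outcomes expected to be significantly better under Quitlink. The items themselves are defined under Covariate or process measures.

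**Motivation.** At baseline a single question asks how strongly the person wants to quit, with the answers "not at all, a little, some, very much". At follow-up a different question offers two alternatives: attempting to give up, or carrying on at the present level. Table 1 marks motivation S at 2, 5 and 8 months, and its key defines S as current smokers.

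**Confidence and self-efficacy.** Table 1 gives these separate rows. Confidence is asked at baseline only: "How confident are you that you can stop smoking for good in the next 2 months if you wanted to". Self-efficacy is asked at 2, 5 and 8 months only: "How confident are you that you will not smoke at all tomorrow". People who have quit at follow-up are given a question about remaining off cigarettes in the long term. The text does not say whether it replaces the next-day question or is added to it.

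**Withdrawal.** The Minnesota scale is described as "an eight item ordinal scale rating withdrawal symptoms from 0 (not present) to 3 (severe"). Then: "At baseline the MNWS is administered, with two symptoms (concentration and appetite) assessed at follow-up". Table 1 agrees: "Minnesota Nicotine Withdrawal Scale (only two items in follow ups").

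**Analysis.** Statistical Methods, under Primary and Secondary Outcomes, specifies a generalised linear mixed model, linear for continuous and logistic for dichotomous outcomes, with baseline as one of four repeated measures. It adds a "sensitivity analysis using a worst case scenario (baseline value for continuous outcomes or relapse for dichotomous outcomes in case of missing value").

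**The concern.** A model that treats baseline as one of the repeated measures needs the same quantity at each visit. For motivation the question and the response format both change after baseline. For self-efficacy there is no baseline value at all.

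The restriction of follow-up motivation to current smokers is a separate and more serious matter. Whether a participant still smokes is what the intervention is meant to change. A comparison among continuing smokers is therefore no longer a comparison of randomised groups, and an arm difference in motivation could reflect who has left the smoking group.

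At stake is part of secondary aim (iii). The trial says it will test these effects and expects significant results, but for motivation its questions cannot give a randomised answer.

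**Working it through.** **1. The protocol's own computed figure.** Inputs from Sample Size Determination: 1% vs 8%, 80% power, p = 0.05 (two-sided assumed), 30% attrition.

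n = (1.960 + 0.842)² × (0.01 × 0.99 + 0.08 × 0.92) / 0.07² = 7.849 × 0.0835 / 0.0049 = 133.75, so 134 per arm. Then 134 / 0.70 = 191.4, given as 191 per arm, or 382 in all.

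The figure reproduces. It uses only the primary outcome, so nothing below affects it.

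**2. The items side by side** (Table 1, Secondary Outcomes, Covariate or process measures).

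| Measure | Baseline | 2, 5, 8 months | Asked of, at follow-up | Same quantity? |
|---|---|---|---|---|
| Motivation | strength of wish to quit, 4 levels | attempting to stop or carrying on, 2 alternatives | current smokers | no |
| Self-efficacy | not asked | confidence of not smoking the next day, 5 levels | marked X, not S | no baseline |
| Confidence | stopping for good within 2 months, 5 levels | not asked | – | separate item |
| Withdrawal | 8 items, 0–3 each | 2 of those 8 items | marked X | yes, if the same 2 items are used |

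**3. Can the stated model be fitted?**
- Motivation: no. A four-level answer at baseline and a two-way answer later fit neither the linear nor the logistic form as one repeated outcome.
- Self-efficacy: only over the three follow-up visits.
- Withdrawal: yes. The full scale would sum to 8 × 3 = 24 and the two follow-up items to 2 × 3 = 6. The same two items were asked at baseline, so a 0–6 score is available at all four visits.

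**4. What the smokers-only restriction could do to motivation.** This is an illustration. Assume:
- the same proportion p in each arm would be trying to quit at 8 months if everyone were counted (no effect on motivation);
- all sustained abstainers come from that proportion;
- they are the only people not smoking.

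With the protocol's rates, 1% of controls and 8% of the intervention arm leave the comparison. Of 134 followed up per arm, that is 134 × 0.01 = 1.3 and 134 × 0.08 = 10.7 people. Among those still smoking, the proportion trying to quit is:
- control: (p − 0.01) / 0.99
- intervention: (p − 0.08) / 0.92

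Difference, intervention minus control = −(1 − p) × (1/0.92 − 1/0.99) = −(1 − p) × 0.0769.

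Under these assumptions p lies between 0.08 and 1. At p = 0.08 the difference is −0.92 × 0.0769 = −0.071. At p = 1 it is 0. So with no true effect on motivation, the smokers-only comparison would lean against the intervention by 0 to 7.1 percentage points. Shorter-term abstainers would also be left out, and their effect is not included.

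**The case against.** **The process-measure heading.** Motivation and self-efficacy are filed as covariate or process measures, while the model is headed Primary and Secondary Outcomes. The list of visits is also clearly generic, since the primary outcome is marked only at 8 months and 7-day abstinence has no baseline mark. The visit list therefore cannot be taken to demand a baseline for every measure, and that part stands. But abstinence needs no baseline measurement, because eligibility requires at least 10 cigarettes a day; motivation has no such known starting value. The heading also does not cancel the Aims and Anticipated Results, which present both measures as expected effects. The sections disagree and need reconciling.

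**The analysis plan could settle it.** This holds for derivation rules, including the withdrawal score. It does not hold for answers that were never requested: no analysis plan can supply a repeated motivation response or a baseline self-efficacy response.

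**Stronger readings that the document does not support.**
- A reader might infer that an eight-item withdrawal total at baseline will be set against a two-item total later. With a constant mean item score m, that would show a fall from 8m to 2m without any change, and baseline fill-in at 30% missing would give 0.7 × 2m + 0.3 × 8m = 3.8m instead of 2m. The protocol nowhere says the eight-item total will be used, and with the matched items both artefacts are zero. The 30% is overall attrition, not a stated rate of missing visits, and with equal missingness the shift would be common to both arms.
- A reader might infer that baseline substitution affects the main results. It is a sensitivity analysis for continuous outcomes. It does not plainly reach a two-way motivation answer, and self-efficacy has no baseline value to substitute.
- A reader might infer that baseline confidence serves as baseline self-efficacy on another scale. Table 1 keeps the rows apart; the response labels are the same and it is the question that differs.
- A reader might infer that quitters and smokers answer different self-efficacy items. The text is unclear, and the X in Table 1 rather than S suggests that everyone gets the next-day question.

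**Conclusion.** The point holds for motivation, and in a narrower form for self-efficacy. The protocol presents both as secondary effects in two sections and as process measures in a third. The items collected do not support the stated four-visit model for either. Motivation is not a repeated measure, and its follow-up comparison is confined to a subgroup defined after randomisation. Its possible size is 0 to about 7 percentage points against the intervention, which rests on the protocol's 1% and 8% and the three assumptions in the illustration; it is not a forecast. Self-efficacy can be compared between arms at follow-up, but not as change from baseline.

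For withdrawal only a clarification is needed: say which items form the score, and do not extend to two items the reliability and validity statement made for the Minnesota scale. The primary outcome and the sample size are not touched.

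**What to change.** - **Status.** Reconcile the Aims and Anticipated Results with Covariate or process measures, so that each of the two measures is either a secondary outcome or a process measure throughout.
- **Motivation.** Repeat the baseline four-level item at each follow-up, or remove motivation from the tested effects and report it as a process measure. Repeating it costs one extra question per call. If it is repeated, state how people who have quit are handled; asking smokers only would repair the measure but leave the subgroup problem. The second option costs nothing in data collection but gives up one stated effect.
- **Self-efficacy.** Analyse at 2, 5 and 8 months only, using the next-day item asked of every participant. Baseline confidence may enter at most as a covariate, with no baseline fill-in. Treat the long-term item as descriptive in quitters. If the next-day item already goes to everyone, this needs only a sentence.
- **Withdrawal.** Define the outcome as the sum of concentration and appetite (0–6) at baseline and follow-up, and name it as two withdrawal symptoms. This needs no new data; the cost is a narrower claim.
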